## Statistical analysis

All statistical analyses will be conducted in the intention-to-treat population based on predefined outcome measures, comparing children treated with each of the two valved holding chambers. Continuous variables with normal distribution will be analyzed using the unpaired *t*-test, and non-normally distributed data using the Mann–Whitney *U* test. Differences in proportions will be assessed with the standard normal deviate (*Z*) test for proportions. Results will be presented as proportions, risk differences, risk ratios, and numbers needed to treat (NNT), each with corresponding 95% confidence intervals (CIs).

*Amended in 25.2.2021, new analysis added: A sensitivity analysis will be performed excluding children with poor cooperation, defined as a mean cooperation score below 4.*

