### Sample Size

Based on previous studies [12],[13] and clinical experience, we estimate that the average RDAI score for children presenting to the emergency department is 11 and that this score decreases to approximately 5 after treatment. The primary outcome is the difference in post-treatment RDAI score between the groups. A difference of at least 2 points is considered clinically meaningful. The sample size is calculated to detect a minimum 2-point difference in final RDAI score (measured at the time of treatment outcome decision) with 90% statistical power ( $\beta$ -error 10%) and 95% confidence ( $\alpha$ -error 5%). The between-group difference in RDAI scores will be analyzed using a t-test, and the standard deviation is assumed to be 2.5 based on earlier studies. Thus, 33 children per group are needed for the final analysis. We anticipate that approximately 15% of enrolled children will be excluded from the analysis due to protocol deviations (e.g., adverse effects, insufficient efficacy, or poor treatment adherence). Therefore, 40 children will be recruited per group, for a total of 80 participants.

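### The protocol fixes a t-test for final RDAI in one section and lets the observed distribution choose the test in another, so neither the primary test nor an estimate in RDAI points is secured

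*Protocol*

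**What the plan says.** The Sample Size section of the Protocol defines the endpoint: "The primary outcome is the difference in post-treatment RDAI score between the groups". It names the test without condition: "The between-group difference in RDAI scores will be analyzed using a t-test". It sets the yardstick, "A difference of at least 2 points is considered clinically meaningful", and the spread: "the standard deviation is assumed to be 2.5 based on earlier studies".

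The Statistical analysis section opens with a scope that includes the primary outcome: "All statistical analyses will be conducted in the intention-to-treat population based on predefined outcome measures". It then makes the test conditional. "Continuous variables with normal distribution will be analyzed using the unpaired" t-test, "and non-normally distributed data using the Mann–Whitney" U test. It makes no exception for final RDAI and does not say which section prevails.

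On reporting, the same section says: "Results will be presented as proportions, risk differences, risk ratios, and numbers needed to treat (NNT"), each with a 95% confidence interval. No mean difference, median difference or location shift is listed.

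**The concern.** Two analysts could each follow the protocol faithfully and run different primary tests. One would take the t-test from the Sample Size section. The other would inspect the RDAI data, judge them non-normal and use Mann–Whitney.

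The choice also affects what is estimated. The trial is sized, and clinical relevance is defined, on a difference in RDAI points. The t-test comes with a mean difference and an interval that can be set against 2 points. The Mann–Whitney U test by itself gives a p-value about ranks. With only binary effect measures named, the protocol would then promise nothing on the scale of its own yardstick.

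Table 3 records that the outcomes were later reduced to a single primary one, the one used for the sample size. Leaving the analysis of that outcome open sits badly with that step.

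**Working it through.** **Inputs (Protocol, Sample Size, unless stated).** Difference δ = 2 points; SD σ = 2.5; power 90%; α = 5% (sidedness not stated); expected final mean about 5; 15% excluded from analysis; 33 per group analysed, 40 recruited. Table 2 gives a whole-point score from 0 to 8 + 9 = 17.

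**1. The plan's own figure.** Two-sided, two means:

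n = 2(z₀.₉₇₅ + z₀.₉₀)²σ²/δ² = 2 × (1.960 + 1.282)² × 6.25/4 ≈ 32.8, so 33 per group.

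This reproduces the stated 33 (one-sided α would give 27). The exact noncentral t calculation gives 33.8, so 34; t-test power is 89.3% at 33, 90.2% at 34 and 94.2% at 40. Allowing for 15% exclusions, 33/0.85 = 38.8 (39) and 34/0.85 = 40. The figure was therefore built on the t-test.

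**2. Sample size under Mann–Whitney.** With normal data the relative efficiency is about 0.955: 33/0.955 = 34.6 (35) and 34/0.955 = 35.6 (36) per group. Both are below the 40 recruited.

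**3. The switching rule.** The protocol gives no normality criterion, so one was assumed: Mann–Whitney if Shapiro–Wilk gives p < 0.05 in either arm, otherwise the t-test. Scores were rounded to integers and limited to 0–17, with SD 2.5 and means 5 vs 5 or 5 vs 7. The underlying shape was either normal or gamma (right-skewed); the gamma shape is also an assumption. There were 5,000 runs per row, so the Monte Carlo standard error of a 5% rate is √(0.05 × 0.95/5000) ≈ 0.3 percentage points.

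| Shape | n per arm | True difference | Mann–Whitney chosen | Significant: t-test | Significant: Mann–Whitney | Significant: switching rule | Tests disagree |
|---|---|---|---|---|---|---|---|
| Normal | 33 | 0 | 23.8% | 4.8% | 4.5% | 4.9% | 1.9% |
| Normal | 33 | 2 | 24.4% | 88.6% | 87.4% | 88.4% | 3.5% |
| Normal | 40 | 0 | 29.6% | 4.9% | 4.9% | 5.1% | 1.9% |
| Normal | 40 | 2 | 28.3% | 94.1% | 93.1% | 93.9% | 2.0% |
| Gamma | 33 | 0 | 87.7% | 4.6% | 4.7% | 4.9% | 2.6% |
| Gamma | 33 | 2 | 80.8% | 88.3% | 91.5% | 91.6% | 5.3% |
| Gamma | 40 | 0 | 93.9% | 4.7% | 4.6% | 4.7% | 2.7% |
| Gamma | 40 | 2 | 88.1% | 93.0% | 95.3% | 95.3% | 3.6% |

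**4. What drives the switch.** At 34 per arm with means 5 and 7, at least one arm fails in about 27% of trials with rounded normal scores and about 26% when the floor at 0 is added. Two independent 5% tests on exactly normal data would already fail in 1 − 0.95² = 9.75% of trials. The rest comes from rounding to whole points; the floor adds nothing, since 0 lies (5 − 0)/2.5 = 2 SDs below the expected mean.

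**The case against.** The strongest reply is that the two sections can be read together. The Sample Size sentence is specific to RDAI, while the Statistical analysis rule is general and must also serve respiratory rate, heart rate and saturation. On that reading the t-test governs the primary outcome. This is reasonable, but the protocol does not say so, and the general rule claims to cover all analyses.

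The list of binary measures follows the sentence on proportions and may be meant only for them. Nothing forbids reporting a mean difference beside a rank test, and a statistical analysis plan may do so. That is fair, and a missing normality criterion or reporting detail is not the finding. The conflict between two statements in this document remains.

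Several stronger readings are tempting but not supported:

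- *The score ends near its floor, so normality will usually fail.* The check in step 4 contradicts this. The high switching rates need a skewed shape that the documents neither state nor imply.
- *The data-driven choice inflates the type I error or costs power.* The simulated rule does neither to any material degree.
- *The test could be picked to favour a device.* The Recruitment and Randomization section has the analysis run under codes A and B, with the devices unknown to the investigators until it is final. That limits any directional choice.
- *The trial could not answer its own question.* An estimate in points remains available from the data; the protocol simply does not commit to it.

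**Conclusion.** The point holds as a conflict between two sections that leaves the primary test, and an estimate with a CI in RDAI points, unfixed. Error rates, power and sample size are barely affected: type I error of the switching rule is 4.7–5.1%, its power is 88–95%, and the two tests reach different conclusions on significance in about 2–5% of simulated trials. The frequency of switching (about 26% with rounded normal scores, over 80% with gamma scores) depends wholly on the assumed Shapiro–Wilk either-arm rule and on a distribution that is not known. It shows that the switch is a realistic possibility, not how likely it is in this trial. The change is worth making because the ambiguity concerns the only primary outcome and is nearly free to remove.

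**What to change.** In the Statistical analysis section, state that final RDAI is analysed, whatever its distribution, as a between-group mean difference with a 95% CI, to be read against the 2-point yardstick. The estimate can come from the t-test already named in the Sample Size section. A linear model adjusted for the baseline RDAI, which is already recorded before treatment, would be preferable, but resolving the conflict does not depend on it; if it is chosen, amend the t-test sentence in the Sample Size section to match. Confine the normality-based rule to the other continuous outcomes, give Mann–Whitney for RDAI as a sensitivity analysis only, and add the mean difference with its CI to the results to be presented. A robust or bootstrap interval is optional.

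The cost is a sentence or two, with no change to the sample size or data collection. It should be settled before the group codes are broken.

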Based on sample size calculations, the study will include 80 children aged 6 months to 4 years who are diagnosed with moderate or severe bronchial obstruction. In the emergency department, the physician-investigator will assess the child's respiratory distress using a standardized clinical scoring tool. Each child will receive salbutamol (0.6 mg or 0.8 mg, based on weight) up to four times at 20-minute intervals via one of the two VHCs. The investigator will assess clinical response at scheduled intervals and determine whether the child should be discharged or admitted for inpatient care. Other aspects of follow-up and treatment will proceed according to standard clinical protocols.

Randomization lists for each site will be created using block randomization with randomly permuted block sizes of 2, 4, and 6. Each child will have an equal chance of being allocated to either VHC group.

Spacer devices are currently used with the assumption that they are interchangeable. However, recent *in vitro* studies suggest that the devices used in Finland may have substantial differences in drug delivery efficiency. One of the main goals of the Finnish National Allergy Program 2008–2018 was to focus efforts on preventing severe symptoms and asthma exacerbations. Respiratory symptoms related to airway obstruction remain a common issue in children, and reducing their frequency and effectively managing acute episodes is key to minimizing both patient suffering and healthcare costs. It is especially important to evaluate, standardize, and optimize critical treatment practices.

The regional ethics committee of the Tampere University Hospital special responsibility area has approved the study on the 18th of March 2019 (Ethics Committee Code: R19030). Recruitment is expected to begin in spring 2019. The results will be published in both Finnish and international peer-reviewed journals.

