## Study Implementation

### Study Design

This study is a randomized, investigator-blinded, multicenter clinical trial conducted in the pediatric emergency departments of Tampere, Oulu, and Kuopio University Hospitals, as well as at the Terveystalo outpatient clinic on [name] in Tampere, Finland. This is a pragmatic therapeutic clinical trial that does not involve blood sampling or any additional diagnostic procedures. Blinding is maintained for physicians involved in the emergency care inhalation therapy and research, for those entering data into the study database, and for the analysts evaluating the study results. The parents, child, and nurse are not blinded, as correct treatment administration requires the nurse to visually monitor the use of the spacer, including the fit of the mask and the movement of the valves in synchrony with breathing. The spacer devices being studied are approved for use in children both in Finland and internationally. The medication administered via the spacer follows the national evidence-based care guideline (Käypä Hoito) [8].

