### Study Procedure from the Patient's Perspective

#### Recruitment and Randomization

When a child aged 6 months to 4 years presents to the emergency department with acute bronchial obstruction, it is first confirmed that the child does not require immediate hospitalization and does not have any of the previously listed exclusion criteria. If eligible, the purpose of the study is explained to the parents, and they are given a patient information sheet to read (Appendix X, which they may keep).

While the parents review the form, the emergency nurse notifies the study unit's investigator, who confirms the diagnosis and the need for treatment. If the investigator is on call, they may personally enroll the child into the study. If the parents decide to participate, they are asked to sign an informed consent form (Appendix Y), of which a copy is also provided to them.

Randomization is conducted by biostatistician [name] (Oulu University Hospital), who is not involved in data collection. First, the spacer devices are coded as either Spacer A or Spacer B. Each center uses block randomization with randomly varying block sizes of 2, 4, or 6 (permuted blocks), as the study is single-blinded (blinding applies only to the study physician).

Randomization to the intervention or control group is carried out by assigning the first available study number between 001–00X to the child. Each participant has an equal probability of being allocated to either spacer group, as the assignment for each study number has been randomly pre-determined per center.

The assigned treatment group is sealed in an opaque envelope, which is opened in numerical order only after written consent has been obtained. The envelopes are prepared by a study nurse who does not participate in data collection. The group codes will not be unblinded until all study-related data has been recorded. Data analysis will be performed using the A and B group codes, meaning the investigators will not know which spacer corresponds to A or B until after the final analysis.

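### Allocation is blocked within each centre, but the prescribed tests ignore centre, so they are conservative and lose precision if centre predicts the outcome

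*Protocol*

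**What the plan says.** On allocation, the protocol Summary states: "Randomization lists for each site will be created using block randomization". The Recruitment and Randomization section repeats this at centre level, with randomly varying permuted blocks of 2, 4 or 6, and adds: "Each participant has an equal probability of being allocated to either spacer group". Centre is therefore a stratification factor with 1:1 allocation inside each stratum. Study Design lists the sites as the "pediatric emergency departments of Tampere, Oulu, and Kuopio University Hospitals, as well as at the Terveystalo outpatient clinic", which makes four strata of two different kinds.

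On analysis, the Statistical analysis section reads "Continuous variables with normal distribution will be analyzed using the unpaired" t-test, then "non-normally distributed data using the Mann–Whitney" U test, and for binary outcomes "Differences in proportions will be assessed with the standard normal deviate" (Z) test. Proportions are to be accompanied by risk differences, risk ratios and numbers needed to treat, each with a 95% confidence interval. The Sample Size section also names a t-test for the primary RDAI comparison. Neither section mentions a centre term, a stratified test or a stratified estimator.

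**The concern.** Blocking within centre forces near-equal numbers on each device in every site. Differences between sites in the average outcome then largely cancel from the device comparison. A pooled test does not know this: its variance estimate includes the between-site spread as if it were random error. The reported standard error exceeds the true one, confidence intervals are too wide and p-values too large.

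This matters only if centre predicts the outcome. That is plausible here. RDAI is scored by the study physician at each site, so differences between raters become differences between centres. The study physician also decides on admission, in three hospital emergency departments and one outpatient clinic. With 40 children per arm, precision on admission is limited in any case, and the stratum is recorded for every child, so ignoring it gives information away.

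**Working it through.** **The plan's own figure.** Inputs from Sample Size: difference 2 RDAI points, SD 2.5, power 90%, alpha 5% (two-sided reproduces the stated number). n = 2 × (1.960 + 1.282)² × 2.5² / 2² = 32.8, so 33 per group, as stated. Allowing for 15% exclusions, 33 / 0.85 = 38.8, so 39; the protocol recruits 40.

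**Continuous outcomes.** The pooled SE at 33 per group is 2.5 × √(2/33) = 0.615. With balanced blocking the true SE is 0.615 × √(1−ρ). The pooled SE is therefore too large by a factor of 1/√(1−ρ), and the actual two-sided alpha is 2 × [1 − Φ(1.96/√(1−ρ))]. Power of the pooled test is Φ[(2/0.615 − 1.96)/√(1−ρ)]; power of the centre-adjusted test is Φ[2/(0.615√(1−ρ)) − 1.96]. ρ is not in the protocol, so the values below are assumptions, and 2.5 is taken as the overall SD.

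| ρ (assumed) | True SE | Pooled SE too large by | Actual alpha | Power, pooled | Power, adjusted |
|---|---|---|---|---|---|
| 0 | 0.615 | 0% | 5.0% | 0.901 | 0.901 |
| 0.05 | 0.600 | 2.6% | 4.4% | 0.907 | 0.915 |
| 0.10 | 0.584 | 5.4% | 3.9% | 0.913 | 0.929 |
| 0.20 | 0.550 | 11.8% | 2.8% | 0.925 | 0.953 |

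Simulating 80 children in four equal centres with blocks of 2, 4 and 6 agrees: at ρ = 0.10 the t-test rejects in 4.0% of null trials without centre and 4.9% with it; at ρ = 0.20, in 3.1% and 5.4%.

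**Admission.** Here ρ = 1 − Σ w·p_c(1−p_c) / [p(1−p)], with w the centre's share of children, p_c its admission rate and p the overall rate. The protocol gives neither centre rates nor a recruitment split (its only figure, in the Introduction, is up to 40% overall). Assume 14, 12, 10 and 4 children per arm and no device effect. For rates of 20/40/60/10%:

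- p = (2.8 + 4.8 + 6.0 + 0.4)/40 = 0.35, so p(1−p) = 0.2275
- within-centre variance = (2.24 + 2.88 + 2.40 + 0.36)/40 = 0.197
- ρ = 1 − 0.197/0.2275 = 0.134, so the SE is 7.5% too large.

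The other rows follow in the same way. The rejection rates come from simulation; the ranges cover exact within-centre balance and blocks of 2, 4 and 6 with incomplete final blocks.

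| Assumed centre rates | SE too large by | Z test rejects (null) | Mantel–Haenszel rejects |
|---|---|---|---|
| 30/40/50/20% | 2.0% | about 4.4–5% | about 5% |
| 20/40/60/10% | 7.5% | about 3.4–4.0% | about 5% |
| 10/40/70/5% | about 18% | about 2.0–2.4% | about 5% |

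If only the clinic differs (40/40/40/10%), the SE is 1.8% too large and the Z test rejects in 4.6%. With no centre effect the two tests agree, so stratifying does no harm to alpha.

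**The case against.** The effect depends wholly on a centre difference that the protocol does not quantify. Common eligibility (RDAI of at least 6, no need for immediate inpatient care), common dose timing and the stated aim of a homogeneous population could all shrink it. Under mild differences the pooled and stratified tests can hardly be told apart. Incomplete final blocks leave some within-centre imbalance, which reduces the deficit further. All of this stands, and it is why the point is conditional.

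The primary comparison loses nothing against its design. With 2.5 as the overall SD, the pooled t-test keeps at least the planned 90% power and forgoes only one to three further points. For admission at 30/40/50/20% and an odds ratio of about 0.3, power is 60.3% with the Z test and 61.5% with Mantel–Haenszel. This also stands.

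A statistical analysis plan, not shown, might add centre. That does not dispose of the point: the protocol does more than stay silent, since it names the tests, and those tests are unstratified.

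A reader might infer that admission must suffer most. The protocol has no figure to support that, and for an equal ρ the proportional overstatement is the same for RDAI and for admission.

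**Conclusion.** The mismatch between stratified allocation and unstratified analysis is in the protocol text and covers all three named tests. Its consequence is conditional: if centre predicts the outcome, standard errors are too large and tests conservative. The size runs from nothing at ρ = 0 to 11.8% at ρ = 0.20 for RDAI, and for admission from about 2% under moderate centre differences to about 18% under extreme ones. All of these rest on assumed centre effects and an assumed recruitment split.

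A reader might take the mismatch to mean that the planned standard errors are certainly wrong, that the comparison is biased, that false positives become more likely, or that the sample size fails. The documents support none of these. The error runs only in the conservative direction, and 33 per group reproduces. This is a worthwhile gain in precision and some power, and should be made; it is not a threat to validity.

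**What to change.** Amend the Statistical analysis section before unblinding, so that adjustment is not a later choice:

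- Final RDAI and other continuous outcomes: a linear model with device and centre as fixed factors, reporting the adjusted difference with its 95% CI.
- Where Mann–Whitney is planned: the centre-stratified rank test (van Elteren).
- Admission, fourth dose and other proportions: centre-stratified Mantel–Haenszel risk differences and risk ratios with 95% CIs and the matching stratified test. Derive the number needed to treat from the stratified risk difference.
- State in advance how a very small centre is handled. If it would be merged with another, justify the choice, because the outpatient clinic is a different kind of site from the hospital departments.
- Align the test named under Sample Size; the number itself need not change.

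The cost is wording, three degrees of freedom and slightly more analysis work. No new data are needed, since centre is known from the randomisation lists.

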## Ethical Considerations

All participants will receive currently recommended treatment. Half of the children will receive bronchodilator medication using the spacer most commonly used in current clinical practice, while the other half will use an officially approved alternative device that, based on *in vitro* studies, appears to outperform the standard device. Both treatments are expected to be beneficial. The study's purpose and significance are explained both orally and in writing, and the parents of all participating children will sign a written informed consent form. Declining participation will not affect the child's medical care. No additional blood samples or painful procedures are included in the study. Any potential adverse events will also be monitored.

The regional ethics committee of the Tampere University Hospital special responsibility area has approved the study on the 18th of March 2019 (Ethics Committee Code: **R19030**). The study will be registered in the *ClinicalTrials.gov* database prior to the enrolment of the first participant. Experts from Fimea and Valvira have reviewed the study. In the CHAMBER study, salbutamol will be used according to its approved indication for patients who would otherwise receive a bronchodilator, and no procedures are performed solely for the purposes of the study. For this reason, no separate notification to Fimea is required. Since both spacer devices are CE-marked and approved for the intended use and age group, no separate notification is required for Valvira either.

